## Abstract

**Background:**

About 10 to 20% of children in West European countries have atopic dermatitis (AD), often as part of the atopic syndrome. The full atopic syndrome also consists of allergic asthma, allergic rhinitis and food allergy. Treatment approaches for atopic dermatitis and asthma include intermittent anti-inflammatory therapy with corticosteroids, health education and self-management training. However, symptoms persist in a subgroup of patients. Several observational studies have shown significant improvement in clinical symptoms in children and adults with atopic dermatitis or asthma after treatment at high altitude, but evidence on the efficacy when compared to treatment at sea level is still lacking.

**Methods/Design:**

This study is a pragmatic randomized controlled trial for children with moderate to severe AD within the atopic syndrome. Patients are eligible for enrolment in the study if they are: diagnosed with moderate to severe AD within the atopic syndrome, aged between 8 and 18 years, fluent in the Dutch language, have internet access at home, able to use the digital patient system Digital Eczema Center Utrecht (DECU), willing and able to stay in Davos for a six week treatment period. All data are collected at the Wilhelmina Children’s Hospital and DECU. Patients are randomized over two groups. The first group receives multidisciplinary inpatient treatment during six weeks at the Dutch Asthma Center in Davos, Switzerland. The second group receives multidisciplinary treatment during six weeks at the outpatient clinic of the Wilhelmina Children’s Hospital, Utrecht, the Netherlands. The trial is not conducted as a blind trial. The trial is designed with three components: psychosocial, clinical and translational. Primary outcomes are coping with itch, quality of life and disease activity. Secondary outcomes include asthma control, medication use, parental quality of life, social and emotional wellbeing of the child and translational parameters.

**Discussion:**

The results of this trial will provide evidence for the efficacy of high altitude treatment compared to treatment at sea level for children with moderate to severe AD.

**Trial Registration:**

Current Controlled Trials ISRCTN88136485.

## Background

About 10 to 20% of children in West European countries are diagnosed with atopic dermatitis (AD) [1]. AD and allergic asthma (AA) are the most common chronic diseases in children. They can be considered different manifestations of the atopic syndrome which also includes allergic rhinitis and food allergy [2]. It has been estimated that 30 to 36% of the children diagnosed with AD aged years or younger will be diagnosed with asthma at age 6 years or older [3]. The reverse has also been demonstrated; in a cohort of children diagnosed with asthma aged between six and nine years, 20% had developed AD after nine years of follow-up [4]. The majority of children with AD are currently treated on an outpatient basis. Treatment approaches include topical treatment with emollients, anti-inflammatory therapy with topical immunosuppressive-like agents (corticosteroids and calcineurin inhibitors), anti-microbial treatment and educational programs, according to current guidelines [5,6].

However, symptoms persist in a subgroup of children with moderate to severe AD. Often these children have an extensive treatment history and are unable to gain sufficient control of their disease. It has been shown that a multidisciplinary approach to AD treatment is beneficial for children who do not respond well to regular treatment, and often results in sustained clinical improvement [7,8]. The multidisciplinary model includes medical and psychosocial evaluation and treatment, and educates the children and their parents using a stepwise approach to the management of AD [8]. Psychosocial evaluation is important because children have to learn to cope with the specific problems associated with living with a chronic disease [9]. Furthermore, they have to learn to adhere to strict medicinal regimes, which are time consuming. Often they are restricted in activities, such as sports, swimming or outside play. Social and emotional problems may occur because of the distinguished appearance and characteristics of AD [10]. Sleep deprivation due to nightly symptoms of itch may lead to tiredness, mood changes and impaired psychosocial functioning of the child and his/her family [10]. AD has a significant negative impact on the quality of life of children and their parents. With increasing AD severity, reported quality of life decreases further [11,12].

Since the 1950s Dutch children with asthma are referred to the Dutch Asthma Center in Davos, located at 1560 m altitude in the Swiss Alps, for ‘high altitude’ treatment [13]. Important characteristics of the alpine climate are the dry air, the low exposure to allergens (such as house dust mite and fungi), and the increased exposure to UV radiation [13]. There is also a relative lack of pollution [14]. Several observational studies have shown significant improvement in quality of life and clinical symptoms (Fev1 (forced expiratory volume in 1 second), FeNO (fraction of exhaled nitric oxide) and SCORAD (scoring atopic dermatitis) among others) in children and adults with AD and asthma after treatment at high altitude [15-21]. However, no randomized trials have been done to investigate the superiority of high altitude treatment compared to treatment at sea level in improving quality of life or disease activity in children with AD or asthma.

In the DAVOS trial, we compare multidisciplinary treatment at high altitude and sea level in a pragmatic randomized design. The objective of this study is to find the most effective treatment strategy for children with difficult to treat AD. This paper describes the study design and the interventions.

## Methods/Design

### Design and setting

A pragmatic randomized controlled trial was designed in collaboration with the Department of Pediatric Dermatology/Allergology in the Wihelmina Children’s Hospital (a national referral center in the Netherlands for children with moderate to severe AD and the atopic syndrome) and the high altitude clinic Dutch Asthma Center Davos in Switzerland. Dutch children with moderate to severe AD are either treated during six weeks at the Dutch Asthma Center Davos (inpatient treatment) or at the Wilhelmina Children’s Hospital (outpatient treatment). All children are expected to be included in the study within a time period of four years.

The trial consists of three different components: psychosocial, clinical and translational. The children in the study will be extensively monitored on these three aspects at study inclusion and during the study period. The study period includes the actual enrollment in the study, a six week intervention period and follow-up measurements at six weeks and six months after the intervention (Figure 1). Enrollment and all follow-up measurements will be done at the Wilhelmina Children’s Hospital. The Digital Eczema Center Utrecht (DECU) will be used for data collection and communication [22]. Within this digital portal possibilities for e-consulting, self-management training and online monitoring are combined.

**Figure 1 F1:**
[figure not shown]
Flowchart of study design.

### Ethical considerations

This study follows the Dutch Medical Research Involving Human Subjects Act 1998 (WMO) and the Helsinki Declaration principles 2008, meaning that the legal representatives of all participants will sign a written informed consent, stating that participation can be withdrawn at any time without any negative consequences concerning their current or future medical treatment. All study procedures have been reviewed and approved by the Medical Ethics Committee of the Utrecht Medical Center, the Netherlands (reference 09-192/K).

### Participants

The DAVOS trial is designed for children in the Netherlands with difficult to treat AD who are unable to gain sufficient control of their disease with current treatment strategies. Children are eligible for enrolment in the study if they are: diagnosed with moderate to severe AD within the atopic syndrome; aged between 8 and 18 years; fluent in the Dutch language; have internet access at home; able to use the Digital Eczema Center Utrecht; and willing and able to stay in Davos for a six week treatment period.

Children are not eligible for enrolment if they are currently participating in another study.

### Recruitment, inclusion procedure and consent

The DAVOS trial is a national trial conducted in the Netherlands. Children with moderate to severe AD will be recruited from the outpatient clinic of the Wilhelmina Children’s Hospital and from other hospitals in the country. Dutch dermatologists, pediatricians, allergists, general practitioners and patient support groups were informed about the trial in journals, conferences and using online media.

Children and/or their parents who are interested in the trial can register themselves directly in the DECU. A questionnaire with items regarding allergic complaints, use of (topical) immunosuppressive therapy such as corticosteroids, and more specific questions regarding AD activity (including a self-administered eczema area and severity index (SA-EASI)), questions on nightly complaints of itch and sleeping behavior and, if relevant, questions on asthma, rhinitis and food allergy complaints has to be answered in order to register. Possible study participants are invited by the dermatologist to the outpatient clinic and assessed for eligibility. They are not required to stop or change their medication at this point. Children who fulfill the inclusion criteria are then informed about the study. If they are interested in participating in the trial, they are invited for a complete evaluation by the multidisciplinary team at the Wilhelmina Children’s Hospital, and informed consent is signed.

### Sample size

The sample size calculation for the psychosocial part is based on the primary outcome coping with itch, measured with the JUCKKI, children’s itching cognitions questionnaire [23]. A difference of five points is expected between the groups on the subscale catastrophisation (negative thoughts that have gone out of control). This difference was based on a study by Staab *et al.* on the effect of educational programs in children and adolescents with AD [24]. In this study, the SD of both groups was 7.6.

An additional sample size calculation was carried out for the clinical part of the trial. This was based on the primary outcome disease activity, measured with the SA-EASI [25]. Based on the study by Staab *et al.*, in which SCORAD was used to measure disease activity, a difference of 10 points between the groups and a SD of 15 for each group was expected [24,26].

With a power of 80%, 36 children are needed in each group. Assuming a drop-out rate of 10%, 40 children will be assigned to each of the two study conditions.

### Randomization

Children are randomly assigned to either intervention or control groups. Randomization is done in SAS (statistical analysis system) with a custom made program by an external data manager using a covariate-adaptive randomization method, controlled for age and diagnosis of asthma [27].

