### Primary and secondary outcomes

The primary outcomes of this study are coping with itch and quality of life of the child for the psychosocial part and disease activity for the clinical part. Coping levels are measured with the JUCKKI questionnaire for children (aged 8 to 12 years) and the JUCKJU questionnaire for adolescents (aged 13 to 18 years) [23]. Quality of life is assessed with the CDQLI questionnaire [30]. Disease activity is assessed with the SA-EASI [25].

Secondary outcomes for the psychosocial part include social and emotional wellbeing of the child, feelings of autonomy and fear, quality of life and stress levels of the parents.

Secondary outcomes for the clinical part include medication use, TARC (thymus and activation-regulated chemokine), total and specific IgE (Immunoglobulin E), asthma control parameters such as FeNO (fraction of exhaled nitric oxide), ACQ (asthma control questionnaire), PAQLQ (pediatric asthma quality of life questionnaire), BHR (bronchial hyperresponsiveness) and spirometric variables such as FEV1 (forced expiratory volume in 1 second), FVC (forced vital capacity) and their ratio (FEV1/FVC). During the follow-up period, the number of flares, the number of dermatologist/pediatric/psychologist appointments, e-consultations and emergency visits or hospital admissions are recorded.

At each time point in the study, questionnaires are filled in by the child and his/her parents, blood samples are taken from the child, and lung function is assessed. A detailed overview of all parameters and measurements is provided in Table 2.

**Table 2 T2:** Study assessments

**Assessment**	**Measured with**	**T-1**	**T0**	**T1**	**T2**	**T3**
Coping with itch and disease	JUCKKI-COPECI (8-12 yr) or JUCKJU-COPEJU (13-18 yr) [23]	x	x	x	x	x
Disease-specific quality of life	CDQLI [31]	x	x	x	x	x
Disease activity and control (AD)	EASI [33]	x	x	x	x	x
	SA-EASI [25]	x	x	x	x	x
	Used topical corticosteroids	x	x	x	x	x
	TARC [34]	x	x	x	x	x
Disease activity and control (Asthma)	ACQ [35]	x	x	x	x	x
	PAQLQ [36]	x				x
	Lung function test	x	x	x	x	x
	FeNO	x	x	x	x	x
	Used medication	x	x	x	x	x
	Metacholine provocation	x	x	x	x	x
Serum	Total IgE		x			x
	Specific IgE: inhalation/food: ImmunoCAP		x			x
	Specific IgE: inhalation/food: ImmunoCAP ISAC		x			
	Eosinophils		x	x	x	x
	Cytokine profile		x	x	x	x
Questionnaires	Social demographic information	x				
	Intelligence test [37]	x				
	SF-36 [38,39]	x				
	CBCL [40,41]	x				
	Corticosteroid use	x			x	x

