### Data collection and data analysis

In this study two sources of electronic data are used. The DECU gives a detailed overview of the intervention and follow-up period and contains the data from the questionnaires, assessments and e-consultations. Additional patient data is extracted from the electronic patient file in the Wilhelmina Children’s Hospital. After data collection, all data will be combined into one SPSS (Statistical Product and Service Solutions) database.

Data will be analyzed on an intention to treat basis. To examine whether there is a significant difference on the primary outcomes between the intervention and control group, a mixed-effects regression model will be used. Fixed effects for time, intervention group and the time*group interaction will be included in the model in order to examine the differences between the groups over time. To adjust for possible curvilinearity a squared term for time will be included in the model. A random intercept and random slope per child will be included in order to account for repeated measures within children. Baseline values of the outcome variables are included as fixed covariates to examine their possible impact on the observed treatment effect.

Data relating to asthma outcomes will be analyzed separately for all children diagnosed with asthma. All analyses conform to a specified plan. There are no interim analyses or stopping rules.

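### Age and asthma diagnosis steer the allocation but are not in the listed primary model, which makes group-level comparisons slightly conservative if these factors predict outcome beyond baseline

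*Protocol article*

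**What the plan says.** The Randomization section describes allocation "using a covariate-adaptive randomization method, controlled for age and diagnosis of asthma".

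The section Data collection and data analysis then gives the primary model term by term:

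- "Fixed effects for time, intervention group and the time*group interaction will be included in the model", with a squared term for time.
- Child-level random effects, namely an intercept and a slope.
- The outcome's own starting value: "Baseline values of the outcome variables are included as fixed covariates to examine their possible impact on the observed treatment effect".

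Age appears nowhere in this list. Asthma appears in that section only to define a subset: "Data relating to asthma outcomes will be analyzed separately for all children diagnosed with asthma". The section also says that analyses follow a specified plan, which is not shown.

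Two other places bear on the point. Under Primary and secondary outcomes, age decides which coping questionnaire a child completes (one for 8 to 12 years, another for 13 to 18). Under Sample size, the trial is sized on differences between groups in points (5 points with SD 7.6, and 10 points with SD 15), with no covariates.

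**The concern.** Covariate-adaptive allocation makes the arms more alike on age and asthma than simple randomisation would. If these factors predict the outcome, the true sampling variance of the group difference shrinks. A model without them leaves their share of the variance in its error term and reports the standard error that simple randomisation would have given. Confidence intervals are then a little too wide, the true type I error falls below its nominal level, and some precision created by the design is not used.

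The factors may well be prognostic. The investigators chose them for balancing, and any difference in scoring between the two coping questionnaires would appear as age-related variance in a primary outcome. That makes age a plausible predictor but does not size its effect. With 72 evaluable children planned, and the Discussion allowing that drop-out may exceed the assumed rate, unused precision has some value.

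**Working it through.** **Inputs.** From Sample size: differences 5 (SD 7.6) and 10 (SD 15), power 80%, 36 per group, 10% drop-out, 40 per group. Assumed, because not stated: two-sided alpha 0.05; and R², the share of outcome variance left after baseline adjustment that age and asthma explain, from 0 to 0.30.

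**Step 1: the plan's own figure.** n per group = 2[SD(1.960 + 0.842)/difference]².

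- Coping: 36.27, so 37 when rounded up; power at 36 is 79.7%.
- Disease activity: 35.32, so 36; power at 36 is 80.7%.
- 36/0.9 = 40.

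The stated size is reproduced to within one child per group. One-sided 0.05 would give 29 and 28, so the two-sided assumption fits.

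**Step 2: effect of leaving the factors out of a group-level comparison.** With the arms balanced on the factors:

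- Reported SE (factors omitted) = SD√(2/n).
- True SE = SD√(2/n) × √(1 − R²).
- True type I error = 2[1 − Φ(1.960/√(1 − R²))].
- Power without the factors = Φ[(difference − 1.960 × reported SE)/true SE].
- Power with them = Φ[difference/true SE − 1.960].

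Example, coping at R² = 0.10: reported SE = 7.6√(2/36) = 1.791; true SE = 1.791 × 0.9487 = 1.699. Power without = Φ[(5 − 3.511)/1.699] = 81.0%; power with = Φ[5/1.699 − 1.960] = 83.7%.

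| R² | Reported/true SE | True type I error | Coping power, without → with | Disease activity power, without → with |
|---|---|---|---|---|
| 0 | 1.000 | 5.0% | 79.7 → 79.7% | 80.7 → 80.7% |
| 0.05 | 1.026 | 4.4% | 80.3 → 81.7% | 81.4 → 82.7% |
| 0.10 | 1.054 | 3.9% | 81.0 → 83.7% | 82.0 → 84.6% |
| 0.20 | 1.118 | 2.8% | 82.4 → 87.7% | 83.4 → 88.5% |
| 0.30 | 1.195 | 1.9% | 84.0 → 91.6% | 85.0 → 92.2% |

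This treats 7.6 and 15 as the SDs in the analysis, so the starting power is about 80%.

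**Step 3: simulation.** 4,000 trials per R², 72 children, minimisation on two binary factors with a 0.8 biased coin, and an endpoint regression with and without the factors. For R² of 0, 0.05, 0.10, 0.20 and 0.30, the unadjusted type I error was 4.8, 4.5, 3.9, 3.2 and 2.0%. Power for the 10-point effect went from 79.4 to 79.5%, 80.0 to 81.6%, 80.9 to 83.8%, 81.5 to 87.3%, and 82.6 to 90.9%. This agrees with the closed form.

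**Step 4: how much is left once baseline is in the model.** Let the factors explain a share f of raw variance equally at baseline and follow-up, and let the baseline–outcome correlation be ρ (assumed 0.4 to 0.7). The share left is f(1 − ρ)/[(1 + ρ)(1 − f)].

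- f = 0.10: 0.048 at ρ = 0.4 and 0.020 at ρ = 0.7. Type I error is 4.5 to 4.8%, and the power gain is 1.0 to 0.1 points for an effect of 10/15 = 0.667 raw SD.
- f = 0.20: 0.107 and 0.044. The gain is 2.1 to 0.2 points.

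These gains are small partly because baseline adjustment alone already lifts power to about 88 to 98% here.

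**Step 5: which model term benefits.** Take a random intercept and slope model with assumed variances (intercept 0.6, slope 0.01, residual 0.4, intercept and slope uncorrelated), visits at 0, 1.5 and 6 months after treatment, 36 per group and complete data. The mean time is 2.5 and the sum of squares about it is 19.5.

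- SE of time by group = √[(2/36)(0.01 + 0.4/19.5)] = 0.0412. The intercept variance does not enter, so main effects of age and asthma leave it unchanged.
- SE of the group difference at the first post-treatment visit = √[(2/36)(0.6(1 − r) + 0.4(1/3 + 2.5²/19.5))], where r is the share of intercept variance due to the factors. It falls from 0.2188 at r = 0 to 0.2110, 0.2030 and 0.1946 at r = 0.10, 0.20 and 0.30.

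**The case against.** The strongest reply has four parts.

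- **The baseline outcome is already in the model.** It may carry most of what age and asthma have to say. This stands and limits the size: Step 4 leaves roughly 0 to 2 points of power for factors explaining 10 to 20% of raw variance.
- **The model is built around time by group.** Adding two factors that are constant within a child does not sharpen that term. This also stands. A reader might infer that all the model's standard errors are too large, but the time by group term shows otherwise. The gain is confined to group differences at a visit or averaged over visits. Those still matter, because the trial is sized on differences in points, not on slopes.
- **Nothing planned is damaged.** A reader might infer that the trial falls short of its power. It does not: the sample size uses raw SDs without covariates, and power without the factors stays between 79.7% and 85.0% at 36 per group over the whole range of R². The error is only in the conservative direction.
- **The unseen plan may add the factors.** It may. But the article does not merely leave covariates open: it names the baseline outcome as a covariate and omits both allocation factors. The mismatch is therefore in what is stated, although it could already be resolved elsewhere.

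**Conclusion.** The mismatch between allocation and model is real, and its consequence is modest and conditional. If age and asthma explain 5 to 10% of the variance remaining after baseline adjustment, group-level standard errors are reported about 3 to 5% too large, the true type I error is about 4.4 to 3.9%, and about 1 to 3 points of power are forgone. At R² of 0.20 to 0.30 the loss would be about 5 to 8 points, but nothing in the article supports values that high. If the factors add nothing beyond baseline, the loss is zero.

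These figures rest on two-sided alpha 0.05, effective balance on both factors, and an assumed R². This is an efficiency gain left unused with slightly miscalibrated inference; it does not invalidate the analysis or the sample size.

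**What to change.** Before the data are analysed, state that the primary-outcome models include age and asthma diagnosis (yes/no) as fixed covariates beside the baseline outcome. Enter age in the form that the allocation program uses. In the asthma-only analyses, where asthma no longer varies, include age. If the specified plan already does this, one sentence saying so settles the point.

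Both variables must be known at allocation, so no new data are needed. The cost is two degrees of freedom if age enters as one term, and slightly more if the program uses more than two age bands.

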### Multidisciplinary treatment

The multidisciplinary team consists of a dermatologist, a pediatric allergist or pediatrician, psychologist and (dermatology/research) nurse. Weekly multidisciplinary evaluation during the intervention between the involved professional teams in Utrecht and Davos takes place using video conference. In this way, expertise is being combined and optimal care for all included patients is guaranteed. A short summary of discussed topics is provided in the patient record in the DECU.

Before randomization and start of the intervention a multidisciplinary treatment plan is developed, with input from both multidisciplinary teams, to make sure the treatment goals can be achieved under either intervention and control conditions. Based on the intake (history of received treatment, psychological questionnaires and intelligence outcomes), specific problem areas are identified and each healthcare professional writes down the treatment goals and strategy in a treatment plan. Psychosocial as well as clinical treatment goals are formulated. Examples of treatment goals are: adherence to treatment; influence and acceptance of AD in everyday life, including distinguished appearance; correct application of topical corticosteroids; coping with itch; sleep disturbances; and knowing what to do during an exacerbation. Planned interventions to achieve the goals are specified, as well as the responsible healthcare professional. There are no treatment restrictions during the trial. The treatment plan is discussed with the child and their parents and may be modified if needed. External professionals who are already involved with the child, for example the referring physician, nurses or social workers, are invited to participate during the study through the DECU, with permission of the child and their parents. In this way, optimal continuation of transmural treatment for the patient is made possible after the end of the study in the home region of the patient.

